### Statistical methods

#### Statistical methods for outcomes

All randomised patients will be analysed by intention to treat, except for those patients whose CVAD insertion is cancelled/failed or who withdraw consent. Continuous data will be reported as means (standard deviation) or median (interquartile limits), as appropriate. Categorical data will be presented as frequency (percentage). The primary outcome, dressing failure, will be investigated using logistic regression with ‘treatment’ as the main effect. Incidence rates of dressing failure, skin colonisation and CLABSI with 95% confidence intervals will summarise the effectiveness of each intervention, and Poisson regression will be used to test for group differences. Kaplan-Meier survival curves (with log rank Mantel-Cox test) will compare dressing failure over time. Other secondary clinical outcomes will be compared between groups with appropriate parametric or non-parametric techniques. *P* values < 0.05 will be considered significant.

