### Who will take informed consent?

Research staff will screen patients according to inclusion and exclusion criteria. If eligible, patients will be approached by research staff for informed consent. If the patient does not have capacity to provide consent, the patient’s substitute decision maker will be approached. If prospective consent is not able to be obtained from either the patient or their substitute decision maker within the inclusion criteria time frame, the patients will be enrolled in the trial under a ‘consent to continue’ model as approved by the reviewing Human Research Ethics Committee (HREC). The patient and/or their substitute decision maker will then be approached for consent either in person (preferred) or by phone as soon as possible after enrolment.

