### Outcomes

#### Primary outcome

Dressing failure: defined as requirement for initial IJ CVAD dressing to be replaced due to the dressing lifting at the edges at any point during CVAD dwell but prior to scheduled dressing change (scheduled dressing changes are every seven days). The requirement for dressing changes will be determined by clinical staff treating the patient, and the clinical indication for dressing change will be recorded. If a patient’s CVAD is removed prior to seven days with the primary dressing still in situ, the dressing will be considered not to have failed.

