### Assignment of interventions: blinding

#### Who will be blinded

Due to the nature of the intervention, blinding of patients/clinicians and research staff to the intervention is not possible. However, the statistician will be blinded for analysis, and microbiology laboratory staff will be blinded when culturing swab growth. The infectious diseases consultant will also be blinded to treatment allocation when apportioning infection outcomes.

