#### Methods in analysis to handle protocol non-adherence and missing data

Prior to analysis, data will be cleaned and attempts at locating missing data will be made. Missing data that is unable to be found will not be imputed prior to analysis. In addition to intention-to-treat analyses, per protocol analyses will also be completed to address protocol non-adherence.

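### The intention-to-treat set drops every patient who withdraws consent, so in an open trial exclusion can depend on arm and on how the dressing performed

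*Protocol article*

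**What the plan says.** Under Statistical methods for outcomes, the protocol article puts all randomised patients into the intention-to-treat analysis "except for those patients whose CVAD insertion is cancelled/failed or who withdraw consent". No distinction is made between a patient who stops taking part and one who refuses use of data already collected.

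Four other sections bear on how this rule works:

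- **Who will take informed consent?** Prospective consent is the default: "If eligible, patients will be approached by research staff for informed consent", and then the substitute decision maker if the patient lacks capacity. A fallback applies "If prospective consent is not able to be obtained from either the patient or their substitute decision maker within the inclusion criteria time frame". The patient is then enrolled under a consent-to-continue model, and the patient or decision maker "will then be approached for consent either in person (preferred) or by phone as soon as possible after enrolment".
- **Who will be blinded.** The article states that "blinding of patients/clinicians and research staff to the intervention is not possible".
- **Primary outcome.** Failure is replacement of the initial dressing because its edges lift, at any time before the scheduled seven-day change. "The requirement for dressing changes will be determined by clinical staff treating the patient".
- **Methods in analysis to handle protocol non-adherence and missing data.** "Missing data that is unable to be found will not be imputed prior to analysis", and per-protocol analyses accompany the intention-to-treat ones.

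**The concern.** Withdrawal of consent happens after randomisation. Here it can happen when the patient, the decision maker and the staff all know the arm, and after the first dressing has been applied and seen to hold or lift. If the decision to withdraw is related to either, removing those patients breaks the balance that randomisation created. A failure recorded before withdrawal would be deleted from the primary comparison, and the result would still carry the name intention to treat.

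There are two routes to this. A consent-to-continue patient may be approached once the allocated dressing is already on. A patient who consented prospectively may withdraw later, having experienced the dressing. The second route exists however often the first is used.

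The per-protocol analysis cannot reveal the problem, because it restricts the set further.

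**Working it through.** **Inputs from the protocol article.** Sample size: 50% control failure, 25% intervention failure, significance level 0.05, 90% power, 77 per group plus 3 for attrition, giving 80 per group. Allocation is 1:1. The number of withdrawals and the share of patients enrolled under consent to continue are not given, so both are assumed below.

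**1. The plan's own figure.** Two-sided test, pooled variance, no continuity correction, mean rate 0.375:

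n = [1.960·√(2·0.375·0.625) + 1.282·√(0.5·0.5 + 0.25·0.75)]² / 0.25² = (1.342 + 0.848)² / 0.0625 ≈ 76.7, so 77 per group. The stated figure is reproduced.

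Power is 91.2% at 80 per group and 90.1% at 77. Loss of numbers is therefore not the issue; selection is.

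**2. Worst case with no true effect (assumed).** True failure is 50% in both arms, so 40 of 80 fail in each. Only failing MLA patients withdraw, w of them, and none withdraw in control. Observed MLA failure is (40 − w)/(80 − w).

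Rejection rate: d = 0.5 − observed MLA failure, SE₀ is the pooled and SE₁ the unpooled standard error with 80 − w and 80 patients, and the rate is Φ[(d − 1.96·SE₀)/SE₁] + Φ[(−d − 1.96·SE₀)/SE₁].

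| w | Observed MLA failure | Spurious benefit | Two-sided type I error |
|---|---|---|---|
| 0 | 40/80 = 50.0% | 0 | 5.0% |
| 3 | 37/77 = 48.1% | 1.9 points | 5.7% |
| 4 | 36/76 = 47.4% | 2.6 points | 6.2% |
| 8 | 32/72 = 44.4% | 5.6 points | 10.5% |
| 12 | 28/68 = 41.2% | 8.8 points | 18.8% |

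For w = 8: d = 0.0556, SE₀ = 0.0811, SE₁ = 0.0810, giving Φ(−1.28) + Φ(−2.65) ≈ 0.101 + 0.004 = 0.105. Simulating the logistic Wald test, with each failing MLA patient withdrawing with probability 20% (about 8 patients), gives 10.4%, of which about 10.0% favours MLA.

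**3. Under the planned effect (50% v 25%).**

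- Removing failing control patients: 3 removed gives 37/77 − 20/80 = 23.1 points; 8 removed gives 32/72 − 20/80 = 19.4 points.
- Removing failing MLA patients: 3 removed gives 40/80 − 17/77 = 27.9 points; 8 removed gives 40/80 − 12/72 = 33.3 points.

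At the planned allowance the shift from 25 points is thus about 2 to 3 points, in either direction.

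**4. Non-differential withdrawal.** If withdrawal is unrelated to outcome, the expected proportions do not change. If 3 failing patients leave each arm, the difference is 37/77 − 37/77 = 0 under no effect and 37/77 − 17/77 = 20/77 = 26.0 points under the planned effect. The bias is nil or about 1 point.

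**5. A result near the boundary (Wald test of the log odds ratio).** Suppose 4 patients per arm are removed and the analysed data are 32/76 control v 19/76 MLA, p = 0.027. If the withdrawn MLA patients had all failed and the withdrawn controls had not, the full data are 32/80 v 23/80, p = 0.14. In the opposite case they are 36/80 v 19/80, p = 0.005. These two extremes bound what the removed patients could do.

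**The case against.** Several points on the other side are sound.

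- **Consent is not generally sought after allocation.** A reader might infer that it is. The consent section makes prospective consent the default and the later approach a fallback whose share is not stated. The point is limited to those patients and to later withdrawals by anyone.
- **Stopping MLA is not an exclusion.** A reader might infer that patients who come off the intervention are lost from the analysis. The documents do not say so. The section on discontinuing interventions ends use of MLA without removing the patient, an omitted application is recorded as a protocol deviation, and non-adherence is handled by a per-protocol analysis. Only withdrawal of consent is at issue.
- **Retention may not be permitted.** A consent-to-continue patient who declines never consented, and the ethics-approved model that governs their data is cited but not reproduced. The fix must leave room for it.
- **A sensitivity analysis may exist elsewhere.** The article condenses a fuller protocol and the analysis plan is not shown, so its silence does not establish that nothing would reveal the effect.
- **The scenarios are extreme.** Nothing in the article says that lifting dressings lead to withdrawal, or that it would happen in one arm only. Eight losses in one arm is well above the allowance of 3.

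What survives is the rule itself. It is stated outright and not left to another document, and it deletes outcomes already recorded without asking whether the patient objects to their use.

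**Conclusion.** The point holds as a modest one. The stated rule allows exclusion from the primary analysis to depend on arm and outcome in an open trial, under a name that suggests otherwise.

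Its size cannot be derived from the documents. With only failing MLA patients withdrawing and no true effect, it is about 2 points at 3 withdrawals (type I error about 5.7%) and about 5.6 points at 8 (about 10.4%). Withdrawal unrelated to arm would leave little or no bias.

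A reader might take the 10.4% as the trial's expected error rate. The documents do not support that: it rests on an assumed one-sided mechanism and on more losses than the plan allows for. The case for change is that the risk is avoidable at almost no cost, not that bias is likely to be large.

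**What to change.** Reword the first sentence of Statistical methods for outcomes on these lines: all randomised patients in whom a jugular device is inserted are analysed in the arm to which they were allocated; data collected up to withdrawal of consent are kept; a patient is removed only if the patient or decision maker refuses use of data already collected, or if the ethics-approved consent model does not allow their use.

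Then:

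- call the resulting set modified intention to treat;
- report the number removed by arm and by consent route (prospective or consent to continue);
- if any are removed, show a best-case/worst-case analysis of dressing failure. Include patients who withdrew with the first dressing intact and its outcome still unknown. Keeping early failures while dropping these patients would tilt the comparison the other way.

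The cost is one line on the withdrawal form separating stopping participation from refusing data use, one small table, and possibly confirmation from the ethics committee that data may be retained. No extra patients or visits are needed.

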**Methods:**

This two-arm, parallel group randomised controlled trial will be conducted in three Australian ICUs. A total of 160 patients (80 per group) will be enrolled in accordance with study inclusion and exclusion criteria. Patients will be randomised to receive either (1) ‘standard’ (in accordance with local hospital policy) CVAD dressings (control) or (2) ‘standard’ dressings in addition to MLA (intervention). Patients will be followed from the time of CVAD insertion to 48 h after CVAD removal. The primary outcome is ‘dressing failure’ defined as requirement for initial CVAD dressing to be replaced prior to seven days (routine replacement).

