### Intervention description

#### Control group

The control group will have their CVAD dressed and secured in accordance with standard hospital policy [17–19] and the individual needs of the participant.

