### Assignment of interventions: allocation

#### Sequence generation

Patients will be randomised in a 1:1 ratio to either ‘standard’ dressing care or ‘standard’ dressing care in addition to MLA. Randomisation will occur in computer-generated randomly varied block sizes of four and six and will be stratified by patient sex to account for facial hair differences.

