Age Weight Height APACHE II Score Skin type • Very fair, fair, medium, olive, etc. Skin integrity • Good, fair, poor Date of hospital and ICU admission ICU admission type • Planned, emergent, IHT Primary reason for ICU admission • Medical, surgical, other Number of comorbidities Current infections • Blood, urinary, respiratory, etc. Current wounds • Yes, no	CVAD insertion site • Left or right IJ Placement of CVAD in IJ vein • High, mid, low Angle of CVAD lumens • Down, up, horizontal Number of CVAD lumens Place of CVAD insertion • ICU, OT, etc. Antimicrobial-impregnated CVAD • Yes, no Inserter type • ICU registrar, ICU consultant, anaesthetic registrar, etc. Number of insertion attempts Technologies used during insertion • Ultrasound, x-ray, ECG, etc. Hair clipped prior to CVAD insertion • Yes, no Dressing site • Neck, chest, other Diaphoretic at insertion site • Yes, no Facial hair at insertion site • Yes, no Dressing and securements in addition to ‘standard care’ • Sutures, bordered transparent dressing, tissue adhesive, etc. Date and time of first MLA application Staff/patient satisfaction with dressing application • 0 = not at all satisfied, 10 = completely satisfied	Date/time of check Reason why check not able to be completed • Patient not available, etc. Is randomised dressing still in situ • Yes, no Dressing site • Neck, chest, other Dressing and securements in situ • Sutures, bordered transparent dressing, tissue adhesive, etc. Condition of current dressing • Clean, dry, intact, lifting at edges, etc. How many edges of the dressing are lifting or requiring reinforcement Complications at CVAD insertion site • Redness, purulent discharge, pain, etc. Has the patient mobilised, been diaphoretic, restless/agitated • Yes, no Signs and symptoms of skin injury/reaction • Pain, itch, redness, rash, papules, stripping, blister, etc. Suspected cause of MARSI or skin injury/reaction Extent of redness, rash or maceration if applicable Positive bloodstream infections since last daily check • Yes, no Number of administration sets What is the CVAD currently being used for • Fluids, blood products, CVP monitoring, blood sampling, etc. Dressing changes since last daily check • Date/time, reason for dressing change, staff/patient satisfaction, etc.	Date/time of CVC removal Reason for CVC removal • Treatment complete with/without complications, patient deceased, routine replacement, etc. Complications at time of CVC removal • Occlusion, unable to aspirate, accidental removal, suspected infection, MARSI, etc. Signs and symptoms of skin injury/reaction • Pain, itch, redness, etc. Extent of redness, rash or maceration if applicable Pain, tenderness, redness, swelling at CVC insertion site Patient mobility at time of CVC removal • Independent, requires assistance, bed-bound, etc. IV antibiotics administered during CVC dwell • Yes, no Patient diagnosed with delirium • Yes, no Staff/patient satisfaction with dressing removal • 0 = not at all satisfied, 10 = completely satisfied	Was the patient alive at 48 h after CVC removal? • Yes, no Date/time of death SAEs Results of CVC tip culture Results of CVC insertion site swabs Results of blood cultures

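### The primary logistic model names treatment only and omits sex, the sole stratification factor, which makes the test somewhat conservative and forgoes a small gain in power

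*Protocol article*

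**What the plan says.** Under Statistical methods for outcomes, the primary analysis is given in one sentence: "The primary outcome, dressing failure, will be investigated using logistic regression with" treatment as the main effect. No covariate, stratification factor or site term is mentioned.

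Under Sequence generation, allocation is 1:1 in "computer-generated randomly varied block sizes of four and six" and "will be stratified by patient sex to account for facial hair differences". Sex is the only stratification factor; site is not one. The Background and rationale section lists beard growth among the causes of jugular dressing failure.

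The trial "will be conducted in three Australian ICUs". Control lines are "dressed and secured in accordance with standard hospital policy", and the intervention arm receives the same policy dressing plus the liquid adhesive.

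The Sample size section asks for 77 patients per group at 90% power and 0.05 significance to detect 50% against 25% failure. It adds three per group for attrition, giving 160 in total.

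**The concern.** The design and the analysis do not match. The protocol constrains allocation on sex because it expects sex to predict the outcome, then states a primary model without sex.

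Stratified blocks keep the two arms almost equal in their share of men, so the difference between the sexes adds almost nothing to the true sampling variation of the treatment comparison. A treatment-only model does not know this. It counts the between-sex variation as noise, and its standard error is too large to the extent that sex matters.

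At stake are a true type I error below 5%, an interval wider than it need be, and a small gain in power that costs no patients.

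A second, smaller mismatch concerns the effect measure. The trial is sized on an absolute difference of 25 points, but the primary model yields an odds ratio.

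**Working it through.** **1. The plan's own figure.** Inputs from the Sample size section: p1 = 0.50, p2 = 0.25, power 90%, alpha 0.05 (taken as two-sided). The pooled two-proportion formula without continuity correction, with mean rate 0.375, is

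n = [1.960 × √(2 × 0.375 × 0.625) + 1.2816 × √(0.50 × 0.50 + 0.25 × 0.75)]² / 0.25² = [1.3419 + 0.8477]² / 0.0625 = 76.7, so 77 per group.

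This matches the protocol. Power by the same method is 90.1% at 77 per group and 91.2% at 80. The trial was therefore sized for an *unadjusted* comparison.

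**2. Hand check of the conservatism.** Assumption: 60% men; the protocol gives neither the share of men nor a sex effect. Take a 50% failure rate in both arms and a sex odds ratio of 5. The rates that satisfy 0.6 × p_men + 0.4 × p_women = 0.50 are 0.652 and 0.272.

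- Variance used by the treatment-only model: 0.50 × 0.50 = 0.250.
- Variance left within sex: 0.6 × 0.652 × 0.348 + 0.4 × 0.272 × 0.728 = 0.2155.
- Ratio: 0.250 / 0.2155 = 1.16. Requiring |z| > 1.96 then amounts to requiring 1.96 × √1.16 = 2.11 on the correct scale, a two-sided rejection rate of about 3.5%.

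The same steps give about 4.7% for an odds ratio of 2, 4.2% for 3 and 2.7% for 8.

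**3. Simulation of the actual design.** 6,000 trials per scenario, 154 patients, blocks of four and six within sex, three equally likely sites not stratified, Wald tests at 0.05. All models were fitted to the same simulated trials. The Monte Carlo standard error of a null rejection rate is √(0.05 × 0.95 / 6000) = 0.3 points.

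Rejection under the null, no site effect:

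| Sex OR | 50% null: treatment only | 50% null: + sex | 37.5% null: treatment only | 37.5% null: + sex |
|---|---|---|---|---|
| 1 | 4.4% | 4.5% | 5.1% | 5.1% |
| 2 | 4.6% | 5.6% | 4.6% | 4.9% |
| 3 | 4.4% | 5.8% | 4.4% | 5.0% |
| 5 | 3.1% | 4.8% | 3.8% | 5.1% |
| 8 | 2.3% | 4.8% | 3.2% | 4.9% |

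Power at 50% against 25%, 77 per group:

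| Sex OR | No site effect: treatment only | No site effect: + sex | Site OR 3: treatment only | Site OR 3: + sex + site |
|---|---|---|---|---|
| 1 | 89.7% | 89.8% | 90.4% | 91.4% |
| 2 | 90.7% | 91.3% | 90.2% | 91.4% |
| 3 | 90.7% | 91.7% | 90.8% | 92.4% |
| 5 | 91.6% | 93.3% | 90.9% | 93.1% |
| 8 | 92.0% | 94.3% | 92.0% | 94.9% |

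The gain is 0.1 to 2.3 points from sex, and 1.0 to 2.9 points from sex and site where sites differ.

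**4. Site alone.** With a highest-to-lowest site odds ratio of 3 and no sex effect, the treatment-only test rejects 4.3% (50% null) and 5.0% (37.5% null). With no site effect it rejects 4.4% and 5.1%. Omitting site leaves type I error where it was.

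**5. Effect measure.** At the design rates the odds ratio is (0.25/0.75) / (0.50/0.50) = 0.33, while the risk ratio is 0.50 and the risk difference 25 points. Once sex is in the model the odds ratio is conditional on sex. With the marginal rates held at 50% and 25% and no site effect, it moves from 0.324 at a sex odds ratio of 2 to 0.266 at 8. The risk difference stays at 25 points.

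**The case against.** **The article does not exclude covariates.** It summarises the model in one sentence, and covariate lists are often left to a statistical analysis plan, which is not shown here. That much is true. But the article chose to state the primary model, and its natural reading is treatment alone. A plan that added sex would change the published analysis.

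**The effect may be negligible.** At sex odds ratios of 2 to 3 the treatment-only test rejects 4.4% to 4.6% under the 50% null, against 4.4% when sex has no effect at all. In that range the shortfall from 5% cannot be put down to omitting sex. The conservatism becomes clear only at stronger effects. It is also in the safe direction: a positive result would remain valid. This objection stands, and it limits the weight of the point.

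**Stronger readings that the protocol does not support:**

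- *A reader might infer that power already paid for is lost.* It is not. The 77 per group is an unadjusted calculation, and the treatment-only test delivers about 90% to 92% in every scenario. What is forgone is an extra gain that the plan never counted on.
- *A reader might infer that omitting site also makes the test conservative, or biases it.* Site is not a stratum, so chance imbalance between sites is random error already covered by the standard error. That dressings actually differ between hospitals is inferred from the reference to local policy; no differences are described, and both arms share the same policy dressing.
- *A reader might want facial hair in the model, since it is the stated reason for stratifying.* In Table 1, "Facial hair at insertion site" is in the CVAD insertion column, beside the first application of the adhesive. Patients may be enrolled before insertion, hair may be clipped, and research staff are not blinded. It could therefore be recorded after allocation by someone who knows the arm.
- *A reader might infer that absolute results will be missing.* The plan already promises percentages and incidence rates with 95% confidence intervals by group. What it does not promise is an interval for the difference in risk.

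**Conclusion.** The point holds in a limited form. As written, the primary model leaves out the trial's only stratification factor, although the protocol's own rationale makes that factor prognostic. The result is a mildly conservative test and interval and a small forgone gain in power. For assumed sex odds ratios of 2 to 8, null rejection runs from 4.6% to 2.3% without sex (50% null), and is about 5% with it (4.8% to 5.8% across those runs). The gain in power is roughly 0 to 2 points, or up to about 3 with site.

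The direction follows from the design. The size depends on assumptions that the protocol does not supply: 60% men, three equally sized sites, and the sex and site odds ratios. The planned 90% power is met either way, and the validity of a positive result is not in doubt. The addition is worth making because it is free and aligns the analysis with the randomisation.

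**What to change.** State, before the data are analysed, that the primary logistic model contains treatment and sex (the stratification factor), preferably with site. Keep the treatment-only model as a sensitivity analysis. With site included the model has five parameters (intercept, treatment, sex, two for site) against 80 × 0.50 + 80 × 0.25 = 60 expected events, which is enough.

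Because the sample size targets an absolute difference, report the risk difference standardised over the covariates, with its 95% CI, beside the odds ratio. Which of the two is the headline is a matter of preference.

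Keep facial hair out of the primary model unless it is recorded before allocation.

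The cost is a sentence or two of wording. Sex is needed to randomise and site is known for every patient, so no data are added. The sample size does not change.

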#### Secondary outcomes

All-cause CVAD failure: a composite of failure resulting in CVAD removal. Includes pain, infiltration/extravasation, blockage/occlusion (with or without leakage), fracture, thrombosis, dislodgement (complete or partial), or haematomaIndividual types of CVAD failure resulting in CVAD removal [pain, infiltration/extravasation, blockage/occlusion (with or without leakage), fracture, thrombosis, or dislodgement (complete or partial)]‘Central line associated bloodstream infection’ defined as per the National Healthcare and Safety Network (NHSN) [20]‘Primary bloodstream infection’ defined as per the NHSN [20]‘Local infection’ as defined by the Centres for Disease Control and Prevention (CDC)/NHSN ‘Arterial or venous infection’ criteria [21]Loss of dressing integrity not requiring dressing change (i.e. lifting at edges with/without reinforcement required) assessed for all dressings per patientDressing dwell time (from dressing application to removal in days) assessed for all dressings per patientPremature dressing removal (before seven days from dressing application; all dressings per patient)Number of dressing changes (from first application to last removal; all dressings per patient)Device dwell-time (time from CVAD insertion to removal in hours)Serious adverse events (i.e. mortality, CLABSI, MARSI)Adverse skin events relating to MARSI (e.g. pain, itch, erythema, skin stripping, blister, skin tear, irritant contact dermatitis, maceration, folliculitis or infection) [22]Cost (cost and number of products used, cost of treating complications, staff time for device insertion), as informed by standard diagnosis related groups (DRGs), staff time estimates to apply and remove dressings and product costs.Staff and patient satisfaction on dressing application and removal (0 = not at all satisfied to 10 = completely satisfied) assessed at initial application, all dressing changes and final removal for all dressing changes per patient.Skin colonization, measured both descriptively (i.e. organism) and quantitatively (i.e. colony forming units)

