### Sample size

A total of 160 patients will be recruited. At 90% power and a significance level of 0.05, 77 patients per group are required to detect a 25% absolute difference in the primary outcome (control failure 50%, intervention failure 25% [2]). To account for potential attrition, three additional patients per group will be recruited.

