**Fig. 1 Fig1:**
[figure not shown]
SPIRIT figure

At the time of CVAD removal, research staff will collect procedural data, in addition to complications and treatment summary data. If able, patient reported satisfaction (see Secondary Outcome 14) will also be collected, in addition to a convenience sample of skin swabs (*n* = 10 per group) to assess skin colonisation under dressings (see Secondary Outcome 15). Patient outcome and adverse event data will be collected at 48 h after CVAD removal.

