### Plans for collection, laboratory evaluation and storage of biological specimens in this trial and future use

Skin swabs will be collected from the area immediately surrounding the CVAD insertion site to assess micro-organism colonisation in a convenience sample of *n* = 10 per group occurring at either CVAD removal or dressing change if the CVAD has dwelled for three or more days. To do this, a sterile dry swab moistened with 0.9% saline will be firmly moved in a twisting back and forwards motion across the area immediately surrounding the CVAD insertion site. The swab will then be placed in a sterile container and transported to a nearby microbiology laboratory to be qualitatively and quantitatively cultured as per standard practice. After analysis, the swabs will be destroyed.

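### Skin colonisation is assigned incidence rates and Poisson regression, but a swab in 10 convenience-sampled patients per arm yields a prevalence or a colony count

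*Protocol article*

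**What the plan says.** All references are to the protocol article.

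- **Analysis.** Statistical methods for outcomes groups three outcomes together: "Incidence rates of dressing failure, skin colonisation and CLABSI with 95% confidence intervals will summarise the effectiveness of each intervention, and Poisson regression" is then named as the test of group differences, with significance at P < 0.05.
- **Outcome.** The last item under Secondary outcomes is "Skin colonization, measured both descriptively (i.e. organism) and quantitatively (i.e. colony forming units".
- **Sample.** Both places that describe the swabs give 10 patients per group, chosen by convenience. The specimen section speaks of the swab in the singular. This implies one per patient but does not say so.
- **Timing, specimen section.** Swabs are taken from the skin around the insertion site, "occurring at either CVAD removal or dressing change if the CVAD has dwelled for three or more days".
- **Timing, Plans for assessment and collection of outcomes.** The paragraph after Fig. 1 opens "At the time of CVAD removal, research staff will collect procedural data". Its next sentence adds the skin swabs to what is collected then. It mentions neither dressing changes nor a minimum dwell.
- **CLABSI.** It is a secondary outcome, and no expected rate is given.

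**The concern.** An incidence rate needs new events counted over time at risk. A swab at one moment shows whether organisms are present and how many. It does not show when colonisation began, and no repeat swabbing is described. The named summary is therefore undefined for this outcome. The named test assumes that the variance equals the mean, which is wrong for a yes/no result (variance smaller) and usually wrong for colony counts (variance larger). Because the protocol itself names the method, an analysis plan that follows it inherits the mismatch.

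At stake is the colonisation comparison, one of several infection-related secondary outcomes. Depending on the coding, it could miss a large difference or declare one that is not there. The primary analysis is unaffected.

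Two smaller matters sit alongside. The two timing statements differ, so swabs may mix occasions and dressing ages. CLABSI may also be rare enough to leave an arm without events.

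**Working it through.** **1. The plan's own figure.** For 90% power at the 5% level, Sample size says that "77 patients per group are required to detect a 25% absolute difference in the primary outcome (control failure 50%, intervention failure 25% [2". Two-sided, pooled variance, no continuity correction, with mean proportion 0.375:

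n = [1.960 × √(2 × 0.375 × 0.625) + 1.2816 × √(0.25 + 0.1875)]² / 0.25² = 76.7, so 77.

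This reproduces. With "three additional patients per group will be recruited" there are 80 per arm. It concerns dressing failure only; no calculation is given for colonisation or CLABSI.

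**2. Colonisation coded yes/no, 10 v 10.** With a and b positives, the plain Poisson Wald statistic is ln(a/b) / √(1/a + 1/b). The correct large-sample variance for two proportions subtracts 2/n. For 8 v 2:

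- Plain Poisson: 1.386 / √0.625 = 1.75, not significant.
- With 2/10 subtracted: 1.386 / √0.425 = 2.13.
- Fisher's exact P: 2 × (2025 + 100 + 1) / 184756 = 0.023.

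Enumerating all 10 v 10 tables, with a zero arm counted as no rejection for Wald:

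| True proportions | Poisson Wald | Fisher |
|---|---|---|
| Equal, 10% to 70% | 0 to 0.12% | 0.1% to 1.3% |
| 50% v 25% | 1.1% | 8.6% |
| 70% v 20% | 11% | 43% |
| 80% v 20% | 21% | 64% |

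The chance that at least one arm has no positives is 58%, 20% and 5.6% at colonisation of 10%, 20% and 30%.

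These Poisson figures are for the Wald test. A likelihood-ratio test from the same model, 2[a ln(2a/(a+b)) + b ln(2b/(a+b))] > 3.84, enumerated in the same way, gives type I error of 0.2% to 7.3% over the same null proportions and 59% power at 80% v 20%. Its error rate varies with the unknown prevalence and can exceed 5%.

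**3. Colonisation as CFU.** The documents give no distribution. Assume a mean of 20 and negative binomial shape k. The variance-to-mean ratio is 1 + 20/k and the plain Poisson standard error is too small by its square root. Approximate type I error is P(|Z| > 1.96/√ratio).

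| k | Ratio | √ratio | Approximate | Simulated |
|---|---|---|---|---|
| 2 | 11 | 3.3 | 55% | 56% |
| 1 | 21 | 4.6 | 67% | 67% |
| 0.5 | 41 | 6.4 | 76% | 75% |
| 0.3 | 67.7 | 8.2 | 81% | 81% |

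**4. Swab timing.** Neither statement mentions study arm. If the swabbed patients mirror their arm, the planning rates of 50% and 25% put at most 10 × 0.50 = 5 control and 10 × 0.25 = 2.5 intervention swabs at an unscheduled first change. This is an upper bound, because changes before three days of dwell do not qualify.

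**5. CLABSI.** Participant timeline expects a mean dwell of 7 days, so exposure is 80 × 7 = 560 catheter-days per arm. At r per 1000 days the expected events per arm are 0.56r. With equal rates, P(at least one empty arm) = 1 − (1 − e^(−0.56r))². The rates are assumptions.

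| r per 1000 days | Expected per arm | Empty arm, equal rates | Empty arm, intervention halves the rate |
|---|---|---|---|
| 1 | 0.56 | 82% | 90% |
| 2 | 1.12 | 55% | 71% |
| 3 | 1.68 | 34% | 54% |
| 5 | 2.8 | 12% | 29% |
| 10 | 5.6 | 1% | 6% |

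**The case against.** **Poisson regression can be fitted to these data.** This stands. Robust variance makes it usable for a yes/no result (type I error 0 to 3.2% in the cases run), and an overdispersion term can address colony counts. A reader might infer that the method cannot be applied at all. The documents do not support that. The narrower fault is that the incidence rate is undefined and that the model as named includes neither correction.

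**The false-positive harm depends on the reading.** This also stands. Inflated error arises only if CFU is the response. The sentence speaks of incidence, which reads at least as naturally as colonised or not, and there the Wald test errs the other way. The protocol does not say which coding or which Poisson test is meant.

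**Poisson is a normal choice for CLABSI.** Agreed. It is an event with catheter-days as exposure. A reader might infer that the CLABSI analysis will often break down, but that rests on a rate the protocol does not give. An empty arm defeats the Wald estimate only; exact and likelihood-based intervals remain, and the protocol does not specify Wald inference.

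**The timing statements may be a short and a full version of one rule.** This is possible, but they still differ on dressing changes and minimum dwell. A reader might infer that the rules themselves treat the arms differently. They do not. Any difference by arm follows only if swabs are taken at dressing changes and the trial's hypothesis is true.

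**Swabbing only at removal would not equalise wear.** This is correct. If controls have more changes, their last dressing may be newer. Consecutive sampling is also awkward with research staff present on business days only and recruitment already under way. Neither is proposed here.

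**Conclusion.** The point holds for skin colonisation. The summary and test that the protocol names do not match the data it describes. The mismatch matters on either coding: type I error of about 0.1% or less and power of 21% v 64% (80% v 20%) for the yes/no Wald test, and about 55% to 81% type I error for overdispersed CFU. The second range rests on an assumed mean of 20 and shape of 2 to 0.3. The first is specific to the Wald test.

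A valid test will not make the comparison informative. Fisher's exact test has 8.6% power for 50% v 25% at 10 per arm, so the result is exploratory whatever the method.

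The swab-timing statements need reconciling; an imbalance by arm is a possibility to monitor, not something the text states. The CLABSI plan is not in error. An empty arm is plausible at assumed rates of 1 to 5 per 1000 days (82% to 12%) and unlikely at 10 (1%), so exact methods are a minor safeguard.

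**What to change.** 1. Remove skin colonisation from the incidence-rate and Poisson sentence. Report the proportion colonised per arm with an exact 95% interval and Fisher's exact test, and CFU with a rank test. Label both exploratory and list organisms descriptively.
2. Reconcile the two statements of when swabs are taken, including whether the minimum dwell applies to both occasions. Record the occasion of each swab (device removal or dressing change) and the days of wear of the dressing above it, and show both by arm.
3. For CLABSI, keep rates per catheter-day. Specify exact Poisson intervals and an exact conditional comparison (given total events, a binomial split by share of catheter-days).

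The cost is a few lines of wording in the protocol or analysis plan, plus one item on the swab record. Dressing-change dates are already collected, so wear time can be derived. No further swabs are required and none already taken need be discarded. As recruitment began in September 2021, a change to the swab wording may have to go through the protocol's amendment route to the ethics committee.
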